# DeintensiF: Standard versus individualized deintensified follow-up after curative treatment in head and neck cancer: protocol of a randomized pilot study

**DOI:** 10.1186/s40814-025-01651-3

**Published:** 2025-05-16

**Keywords:** Follow-up studies, Head and neck neoplasms, Squamous cell carcinoma of head and neck, Neoplasm recurrence, Local, Recurrence, Precision medicine, Patient-reported outcome measures

## Abstract

**Background:**

Around 70% of head and neck cancer (HNC) cases are diagnosed in an advanced stage. Improvements in treatment have led to a cure rate of up to 80–90% for early-stage and 40–50% for advanced-stage disease. However, routine follow-up involves social and financial burdens, including frequent imaging associated with radiation exposure and costs. Currently, there is no consensus on the follow-up strategy after HNC treatment, and no conclusive evidence shows a survival advantage for routine follow-up over symptom-driven self-referrals. The DeintensiF study aims to provide robust evidence, comparing standard follow-up with a tailored deintensified approach. Additionally, it seeks to explore whether early detection of recurrence/second primary malignancy in asymptomatic patients impacts survival and quality of life. The pilot phase aims to assess feasibility of patients’ recruitment and adherence to the assigned follow-up strategy and patient-reported outcomes (PROs) questionnaire in the first 2 years.

**Methods:**

This randomized-controlled, multicenter, open-label, pilot study has the goal to randomize a minimum of 16 patients across three Swiss sites into two arms within 1 year. The Experimental Arm A: scheduled clinical exams every 6 months and monthly PRO with evaluation and possibility to alert for open urgent appointments; and the Control Arm B: regular visits every 3 months for the first 2 years and less frequent thereafter plus multiple scheduled imaging appointments for head and neck magnet resonance imaging (MRI) and computed tomography (CT) with contrast and chest CT scans. Patients’ motivation for participation or not will be explored by additional questionnaire before randomization. The primary objective during the pilot phase is to evaluate the feasibility of recruiting and randomizing patients with complete remission 6 months after treatment of head and neck squamous cell carcinoma to a deintensified and to a conventional follow-up. The secondary objective is to assess adherence to the two different follow-up strategies.

**Discussion:**

If feasible, the DeintensiF pilot study will expand from the recruited patients (detailed in the “Methods” section) to a larger cohort of advanced HNC cases in the main trial, integrating electronic PRO tailored follow-up care. This approach aims to reshape follow-up practices, enhancing patient-centered strategies and outcomes in head and neck oncology.

**Trial-registration:**

ClinicalTrials.gov (NCT05388136); Swiss National Clinical Trial Portal (SNCTP000005198).

**Supplementary Information:**

The online version contains supplementary material available at 10.1186/s40814-025-01651-3.

## Background and rationale

Head and neck squamous cell carcinoma (HNSCC) are the 6 th most common type of non-skin cancer [1]. Tobacco, alcohol, and human papillomavirus (HPV) are the main risk factors. Treatment options vary from surgery to radiotherapy (RT), either alone or combined with chemotherapy (CXRT), tailored to cancer site and stage. Early-stage HNSCC (stages I–II, 30% of cases) typically receive single-modality treatment, while advanced cases (stages III–IVA/B, 70% of cases) often necessitate multimodal approaches, such as CXRT or surgery followed by adjuvant (CX)RT. Cure rates for early-stage cancer reach 80–95%, yet locoregional recurrence (REC) affects 50–60% of advanced cases within 2 years, with 20–30% developing distant metastases. Additionally, there is a + 2–4%/year risk of second primary malignancies (SPM), mainly in the lung (60%) and superior aero-digestive tract (20%). HPV-positive oropharyngeal cancer patients exhibit lower REC/SPM risks [2–9]. The 5-year overall survival rates for HNSCC patients treated between 2002 and 2006 averaged 65.9% [10]. Despite treatment successes, patients face treatment-related morbidities, impacting their quality of life (QoL), necessitating comprehensive follow-up (FU) protocols. Curative setting patients’ FU in this population includes treatment response evaluation, REC/SPM detection, management of treatment sequelae, nutritional restoration, and psychosocial support [11]. Unnecessary investigations that may cause morbidity, discomfort, or stress and may add financial burden on the patient need to be avoided. There is neither consensus nor level one evidence on how to ideally achieve these globally accepted FU goals. Guidelines recommend routine clinical visits for head and neck examination, assessing radiation-induced toxicity and functional rehabilitation [12]. Following baseline imaging (magnet resonance imaging (MRI) and computed tomography (CT)) within 3–4 months post-surgery or after definitive CXRT, long-term reimaging until and beyond 5 years in asymptomatic patients remains controversial and unexplored. Within 3–6 months post-CXRT, a hybrid positron emission tomography CT or MRI (PET) is recommended for treatment response assessment and detection of tumor persistence/progression [13]. A chest CT scan should be performed if chest imaging is requested (chest X-ray detects only 33% of intra-thoracic lesions visualized by chest CT) [14]. Existing FU approaches lack consensus, varying in visit frequency, imaging, and duration, as listed in Table 1 [15–25].

**Table 1 Tab1:** Published guidelines on FU intervals

Period	Year 1	Year 2	Year 3	Year 4	Year 5	> 5 years
*Guidelines*						
ASHNS (ASHNS, 1999) [15]	1–3	2–4	3–6	4–6	4–6	12
BAHNO (BAHNO, 2001) [16]	1–1.5	1–1.5	3	6	6	12
DCHNO (DCHNO, 2002) [17]	2	3	4	6	6	–
Lester and Wight, 2009 [18]	1	2	3	4	6	12
Digonnet et al., 2013 [12]	2–3	2–3	3–6	3–6	6	12
AIMO/AIRO (AIMO/AIRO, 2016) [19, 20]	1–3	3	3–6	6	6	12
FOS (FOS, 2016) [21]	2	3	4	6	6	12
SSORL (SSORL, 2019) [22]	1–3	1–3	4–6	4–6	4–6	(12)
EHNS/ESMO/ESTRO (EHNS/ESMO/ESTRO, 2020) [23]	2–3	2–3	6	6	6	12
NCCN (NCCN, 2024) [24]	1–3	2–6	4–8	4–8	4–8	12

Suggested interval of FU visits in months by selected authors and national committees

*AIMO* Associazione Italiana Oncologia Medica, *AIRO* Associazione Italiana Radioterapia Oncologica, *ASHNS* American Society of Head and Neck Surgeons, *BAHNO* British Association of Head and Neck Oncologists, *DCHNO* Dutch Cooperative Head and Neck Oncology Group, *EHNS* European Head and Neck Society, *ESMO* European Society for Medical Oncology, *ESTRO* European Society for Radiotherapy and Oncology, *FOS* French ORL Society, *NCCN* National Comprehensive Cancer Network, *SSORL* Swiss Society of Oto-Rhino-Laryngology, Head and Neck Surgery

Routine surveillance has shown survival benefits in two retrospective studies for REC diagnosed during scheduled FU visits compared to self-referral [26, 27]. However, many other retrospective studies found no difference in overall survival (OS) between routine FU and symptom-driven self-referral, indicating that patients efficiently detect symptomatic REC while silent RECs are rare [28–42]. Additionally, electronic Patient-Reported Outcomes (ePROs) enable real-time symptom monitoring and may offer a survival benefit. Basch et al. (2016) demonstrated that web-based ePROs significantly enhanced 1-year survival rates for advanced solid cancer patients [43]. Another study showed that ePROs during chemotherapy for advanced lung cancer increased 2-year survival, surpassing standard post-treatment imaging for REC detection [44]. With limited evidence on post-treatment FU for HNSCC patients, a multicenter trial comparing deintensified and conventional FU strategies is crucial to establish a cost-efficient, patient-centered approach.

The DeintensiF main trial hypothesizes that a patient-centered deintensified and individualized FU strategy is non-inferior compared to a standard FU approach. The specific primary aim of the DeintensiF trial is to determine whether the new approach with enhanced patient involvement actually reduces the number of outpatient visits without compromising survival compared to a standard FU with fixed scheduled clinical exams and imaging in curatively treated HNSCC patients. Secondary objectives relate to investigating additional clinical and economic effects of the deintensified individualized FU scheme. In addition, we aim to disentangle underlying mechanisms and to describe implementation aspects including acceptance and patient views. For the full protocol, see Additional file 1: DeintensiF-Full Protocol.

The general aims of the DeintensiF pilot phase are to evaluate the feasibility of recruiting and randomizing patients with complete remission 6 months after treatment of HNSCC to a deintensified or conventional (standard) FU. The secondary objective is to investigate adherence to the two different FU strategies. Good compliance is defined as the realization of the planned/organized visits and exams at the planned time ± 4 weeks as well as regularly recording of signs and symptoms in the PROs questionnaire.

## Methods

### Trial design

Patients fulfilling the eligibility criteria are randomized to one of two FU schedules using a 1:1 ratio. The study also investigates patients'adherence to the assigned protocol and collects additional data on patients’ motivation for study participation. Three Swiss academic tertiary referral centers in Bern, Lucerne and Zurich are involved in this initial phase. During the pilot phase, the sites committed to enroll a total of 20 patients within the first year. This phase serves as a crucial precursor to the main trial, providing insights into the practicality and effectiveness of the deintensified FU strategy compared to the standard approach. The pilot study differs from the main study by collecting additional data concerning patients’ motivation for study participation and the use of paper-based symptom reporting in the experimental arm (as opposed to an electronic patient-reported outcome data capture system). Otherwise, all procedures mimic the main trial. Data from this pilot study will be used to inform the planned large-scale main trial. Decisions will be based on a traffic light system (Fig. 1) before implementation of the larger-scale main trial, demonstrating its feasibility and relevance in addressing the challenges of post-treatment FU in HNSCC patients [45].

**Fig. 1 Fig1:**
[figure not shown]
Traffic light system for moving from the pilot phase to the main phase. *Green: continue (i.e., no concerning issues that threaten the success of the trial); yellow: either adapt or continue with caution (i.e., remediable issues); red: stop or at least halt (i.e., intractable issues that cannot easily be remedied). Although it is foreseen to have only two to three sites in the pilot, using enrolment in the two best enrolling sites allows also for more sites in the pilot

The success of the pilot study and its progression to the main trial depend on observed enrolment rates and adherence to the FU protocol, as demonstrated in Fig. 2. The criteria for advancing to the main trial are based on the number of sites planned for participation, the size and duration of participation of those sites, and an expected enrolment of 550 patients within 3 years for the main trial.

**Fig. 2 Fig2:**
[figure not shown]
Flow chart of participants’ recruitment and study procedure of the main trial. Abbreviations: IC = inclusion criteria; mths. = months; RMST = restricted mean survival time; SPM = second primary malignancy; TX = treatment; wks. = weeks

### Objectives and success criteria of the pilot study

#### Primary objective

The primary objective is to assess the feasibility of recruiting and randomizing HNSCC patients in complete remission 6 months post-treatment to either a deintensified or a conventional FU protocol. The aim is to recruit at least 80% of the committed 20 patients (*n* = 16) within the initial 1-year recruitment period, ensuring that enrollment remains on track to achieve sample size and timeline goals.

#### Secondary objective

The secondary objective is to investigate adherence to the two FU strategies, defined as the completion of scheduled visits and exams as planned, along with regular recording of signs and symptoms in the patient-reported outcomes (PRO) questionnaire. Good compliance is defined as the realization of the planned/organized visits and exams at the planned time ± 4 weeks as well as regularly recording of signs and symptoms in the PRO questionnaire. A retention target of 90% is set for those completing scheduled FU assessments, alongside an adherence goal of 85% to the FU schedule. To ensure the reliability of the findings, at least 95% completeness is aimed in required data fields, with data audits conducted by the Clinical Trials Unit at the University of Bern.

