#### Study intervention

Patients in the experimental arm will have scheduled outpatient visits every 6 months including a clinical examination. In-between, patients complete a monitoring questionnaire monthly, with alerts triggering additional visits, if necessary. Details of the instrument are shown in Table 2. Participants will receive reminders to complete the PROs questionnaire the day before the expected date with up to three reminders in the main study, if missed. During the pilot study, phone calls are conducted if the PROs questionnaire is completely or partially missing 1 day after the planned date, which mimics the automated alert by the app in the future main study. In the main trial, a phone call will also follow 3 days after the app’s notification, in case the questionnaire is still not completed. Patients not able to adequately use the app will be offered a paper-based version of the PROs questionnaire, similar to the pilot study. The use of a paper-based PRO questionnaire in the pilot study is a logistical choice intended to simulate the future electronic alert system. This change is solely for feasibility assessment, and any potential differences in data collection methods will be controlled in subsequent subgroup analyses. If a patient fails to complete the PRO, up to two calls are made within 1 week to gather the results. Depending on the rating, the PRO will trigger an alert, manually by phone call during the pilot phase or automatically through an electronic alert in the main study. The alert will recommend an earlier control visit if the patient’s conditions indicate a possible REC/SPM, with the center scheduling an “open urgent appointment” within 2 weeks.

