**Table 2 Tab2:**
[figure not shown]
Patient reported outcome questionnaire (symptom tracker)

Patients in the control arm will have scheduled outpatient visits with clinical examination every 3 months (years 1–3) and every 6 months (years 4–5). In addition, patients will undergo scheduled imaging 6 and 18 months after enrollment. Smokers will have additional chest CT-scans 30, 42, and 60 months after enrollment. In the conventional arm, participants will also complete the PROs questionnaire monthly and during every visit, but neither participant calls will be made nor alerts will be sent.

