**Table 3 Tab3:**
[figure not shown]
Study assessment schedule

Participants will undergo comprehensive imaging, including head and neck MRI or CT scans and contrast-enhanced trunk CT scans, at 3 to 6 months, and at 6 and 18 months post-randomization, to confirm remission and detect secondary primary malignancies (SPM). Annual low-dose chest CT scans without contrast will be performed on current or recent heavy smokers from 18 months to 5 years, per National Comprehensive Cancer Network (NCCN) Guidelines [13, 24]. Adverse events will be monitored using Common Terminology Criteria for Adverse Events (CTCAE) v.5.0. Medical interactions, including unscheduled visits and supportive treatments, will be recorded via a Concomitant Care Questionnaire. Compliance with FU visits and symptom monitoring using paper or electronic PRO questionnaires will be tracked. Health care utilization costs, including FU visits, imaging, and personnel expenses, will be documented.

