In the main study, analysis sets are defined in line with estimands, including intention-to-treat and two per-protocol sets. The intention-to-treat set will consist of all randomized participants, regardless of protocol violations, while the per-protocol sets will define adherence differently: (a) “while-on-treatment” excludes non-adherence due to medical reasons, and (b) “hypothetical” includes any non-adherence. Adherence will be calculated based on scheduled visits completed within a ± 4-week window, with classification occurring only before REC/SPM occurrence. The main study’s primary endpoint, 5-year restricted mean survival time (RMST), and secondary endpoints will be analyzed using mixed-effects and negative binomial models, with adjustments for competing events [51–55]. A cost and cost-utility analysis will be performed if the trial shows promising non-inferiority results. This analysis will compare the incremental cost-utility ratio of the deintensified versus standard FU, using quality-adjusted life years (QALYs) and standardized healthcare costs.

For detailed procedures and analysis methods, refer to the full protocol submitted as supplementary material (see Additional file 1: DeintensiF-Full Protocol).

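### The pilot's adherence measure counts missed care but not excess care, so neither it nor its 85% goal can flag failed de-intensification in Arm A

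*Protocol article*

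**What the plan says.** The Secondary objective section of the protocol article describes "adherence to the two FU strategies, defined as the completion of scheduled visits and exams as planned". A second element follows in the same sentence, namely PRO recording by the patient. The standard for good compliance is the "realization of the planned/organized visits and exams at the planned time ± 4 weeks" together with regular PRO recording, and the target is "an adherence goal of 85% to the FU schedule". The last paragraph of Background and rationale gives the same definition of good compliance. For the main trial, the Statistical analysis section says "Adherence will be calculated based on scheduled visits completed within" a window of ± 4 weeks, up to recurrence or second primary malignancy (REC/SPM).

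On the schedules, Study intervention states: "Patients in the experimental arm will have scheduled outpatient visits every 6 months including a clinical examination". Arm B is seen every 3 months in years 1 to 3 and every 6 months in years 4 and 5, with imaging at 6 and 18 months. Both arms fill in the PRO monthly.

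On data capture, Detailed study procedure states: "Medical interactions, including unscheduled visits and supportive treatments, will be recorded via a Concomitant Care Questionnaire". Follow-up visits and imaging are also documented for costs.

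The text under Fig. 1 makes progression depend on enrolment and on adherence to the follow-up protocol. Endpoints of the pilot study adds that meeting the targets will confirm feasibility.

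**The concern.** Arm A consists largely of giving less follow-up, and Background and rationale names fewer outpatient visits as part of the main trial's specific primary aim. The obvious way for such a strategy to fail is that centres go on seeing Arm A patients at the usual frequency. This is plausible here. The trial is open-label, and all ten guidelines in Table 1 have year-1 visit intervals of 3 months or less.

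The adherence rule subtracts only for scheduled items that did not happen. If continued routine surveillance in Arm A leaves the score at 100%, the pilot can meet its adherence goal with no contrast in visits between the arms. In the non-inferiority main trial the same drift makes the arms alike, which favours a non-inferiority conclusion.

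**Working it through.** The 85% is a set target, so there is nothing to reproduce. The nearby recruitment figure does reproduce: 0.80 × 20 = 16. With 1:1 allocation this gives 16/2 = 8 to 20/2 = 10 patients per arm.

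**Inputs**
- Arm A visits at months 6, 12, …, 60 (Study intervention).
- Arm B visits at months 3, 6, …, 36, then 42, 48, 54, 60 (Study intervention).
- Window of ± 4 weeks (Secondary objective).
- Adherence monitored until the last participant completes 12 months, in the second year (Statistical analysis). Months 12 and 24 are therefore the relevant horizons for the pilot.

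**Step 1: score each crossover with the stated rule.** Visit adherence = scheduled visits of the assigned arm completed in the window ÷ scheduled visits of that arm. Every Arm A date is also an Arm B date. The Arm B dates that Arm A lacks lie 3 months from the nearest Arm A date, outside the window.

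| Horizon | Arm A visits scheduled | Arm B visits scheduled | Arm A patient on Arm B calendar | Arm B patient on Arm A calendar |
|---|---|---|---|---|
| 12 months | 2 | 4 | 2/2 = 100% | 2/4 = 50% |
| 24 months | 4 | 8 | 4/4 = 100% | 4/8 = 50% |
| 60 months | 10 | 16 | 10/10 = 100% | 10/16 = 62.5% |

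The abstract has 3-monthly visits for 2 years only. Arm B then has 14 visits by month 60 and the last cell becomes 10/14 = 71%. The 12- and 24-month rows do not change.

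**Step 2: the PRO component.** Both arms complete the PRO monthly, so an over-followed Arm A patient can meet this part too. It does not separate the schedules.

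**Step 3: what a measure of excess would show.** By month 12 the over-followed Arm A patient has 4 − 2 = 2 extra visits, and by month 24, 8 − 4 = 4. If imaging belongs to Arm B only, there is also 1 extra imaging round by month 12 and 2 by month 24. The article does not say whether the 85% is scored per patient or per visit. Assuming per patient, with k over-followed patients among n in Arm A and all else complete, the two-sided score is (n − k)/n:
- n = 10: k = 1 gives 90%, k = 2 gives 80%.
- n = 8: k = 1 gives 87.5%, k = 2 gives 75%.

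Two such patients take the arm below 85%. Under the stated rule the score is 100% for any k.

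**Step 4: main-trial dilution.** If a share c of Arm A effectively receives control follow-up and has the control outcome, the intention-to-treat difference is about (1 − c) times the true one. For c = 10% this is 90%, and for c = 30% it is 70%. The range for c is an assumption, since the article gives no contamination rate.

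**The case against.** A reader might infer three stronger things that the article does not support.

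- *That adherence consists of visits and exams alone.* It does not, because PRO recording is part of the pilot definition. Step 2 shows that this does not rescue the measure.
- *That the pilot cannot detect failed de-intensification at all.* It could. Unscheduled visits go into the Concomitant Care Questionnaire, PRO-triggered and self-referral visits are documented as concomitant care events, and visits and imaging are documented for costs. Visit numbers are also part of the main trial's aim. What the text lacks is a rule or progression target that uses these data.
- *That the main trial's per-protocol sets would certainly keep over-followed patients.* One condensed sentence on calculation cannot carry that. The article sends detailed methods to the full protocol, and one per-protocol set is described as dealing with any non-adherence.

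It can also be argued that the wording of the pilot endpoint, adherence to the randomized schedule, could be read to cover excess, and that Fig. 1, Table 3 or the full protocol may hold the rule. This limits certainty. It does not remove the point, because the definition given in the article is explicit and runs in one direction only.

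A further objection concerns the remedy. Clinicians may add visits for the patients who worry them. Excluding those patients from Arm A could leave a better-prognosis group and itself favour non-inferiority. That objection stands, and the fix respects it.

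**Conclusion.** The point holds in a bounded form. As defined in Background and rationale, Secondary objective and Statistical analysis, adherence runs in one direction. Full control-type follow-up in Arm A can score 100% (2/2 visits by month 12, with 4 made), while the reverse crossover scores 50% on visits. The adherence endpoint and its 85% goal therefore cannot flag failed de-intensification, although the data to do so are collected.

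The visit result needs no assumption beyond the stated schedules and window. The imaging part is less certain: Study intervention gives imaging at 6 and 18 months to the control arm, whereas Detailed study procedure gives it to participants without naming an arm. If it applied to both arms, that contrast would disappear and the visit contrast would remain. The effect of two patients on the 85% goal assumes per-patient scoring, and the dilution figures assume c. This should be corrected before the pilot's adherence result is used for progression.

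**What to change.** In the last paragraph of Background and rationale and in Secondary objective, add a second, separately reported adherence component for Arm A. It counts clinician-initiated visits or surveillance imaging before REC/SPM that were not scheduled for the arm and not triggered by a PRO alert, a symptom, a self-referral or an adverse event. Alert-triggered and self-referral visits stay adherent, because the strategy provides for them. Derive the component from the concomitant care and utilization data, show visit and imaging counts per arm, and consider both in the traffic-light decision alongside the 85% goal.

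For the main trial, report the same measure by arm next to the non-inferiority result. Use it at most in a sensitivity analysis, because exclusion on post-randomization behaviour may introduce selection bias.

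Reconcile Study intervention with Detailed study procedure on which arm has imaging at 6 and 18 months, and the abstract with Study intervention on how long the 3-monthly visits last.

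The cost is a wording change, one derived variable and possibly a reason-for-visit field. Measured Arm A adherence may look lower. The reason for each visit must also be classified, which involves judgement in an open-label trial, so the categories should be fixed in advance. If the full protocol or Fig. 1 already contains such a rule, it is enough to state it in these sections.
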